## 1. Introduction

Atherosclerosis is a systemic disease, and also known as Arteriosclerosis or hardening of the arteries, in which lipid, or fatty deposits, plaque, inflammation, cells, and scar tissue build up within the walls of small and large arteries supply to a variety of end-organs, it includes mainly the heart, brain, kidneys, and extremities (Benjamin et al., 2017). There are several risk factors, which is mainly focused on traditional and non-traditional (Martin-Timon et al., 2014) traditional risk factors are obesity (Nadeau et al., 2014), overweight, physical inactivity, active and passive smoking (Steinberger et al., 2016), tobacco use, consumption of alcohol, high caloric diets, sedentary lifestyle, stress, hypertension, diabetes mellitus, dyslipidemia, sleep apnea, lack of estrogen in women, urbanization, and modernization (Al Makadma, 2017; Martin-Timon et al., 2014; Smetzer et al., 2010). Non-traditional risk factors are family history/genetics (Jaemon et al., 2017), aging, gender (more often in male than females), race/ethnicity, hyperinsulinemia, postprandial hyperglycemia, glucose variability, thrombogenic factors, inflammation C-reactive protein, and homocysteine (Martin-Timon et al., 2014; Smetzer et al., 2010). One of the associated factor lower socio-economic status during adolescence significantly predicted greater adult CVD risk through the following pathways: health behaviors, financial stress, lack of medical/dental care, and educational attainment (Doom et al., 2017). Study reported that higher systolic blood pressure, and low-density cholesterol, and lower level of high-density cholesterol in young adulthood associated with atherosclerosis and high carotid intima-media thickness (Benjamin et al., 2017).

An adolescent may consider as an individual in the 10-19 years and categorized age group into three stages: early (~10 - 14years), middle (~15 - 17years), and late adolescence (~18 - 21years) (World Health Organization, 2020) Around 1.2 billion people of the world's population are adolescents aged 10 to 19 years (World Health Organization, 2017). Adolescence is a critical and complex, often considered healthy period of life, and time of remodeling of the brain's reward system (Patton et al., 2016). It is a period of transitional changes takes place in biological, physical, psychological, socio-cultural, and emotional changes, and considers very important foundation for the future of both individuals and nations (Taylor et al., 2016; World Health Organization, 2020). It is a time period where many characteristics of good, positive health are at their height, they may have fewer needs than those in early childhood or in later years (Patton et al., 2016; Taylor et al., 2016).

In middle to late adolescence stage, many cognitive abilities increase markedly, and start to decrease before the age of early 30s. In this phase in adolescent brain development brings various skills like self-regulatory, intellectual, decision making, and problem solving skills leading to greater future orientation (Patton et al., 2016). Adolescent health is influenced by their environment, education, supportive relationships, stakeholders, and access to high quality health services. We must create the opportunities to meaningfully engage with them in all aspects of their healthy lives, therefore reduce the adolescent health risks for later-life non-communicable diseases will require an unprecedented extent of coordination across sectors from the global to the local level (Patton et al., 2016).

Education is a powerful determinant of adolescent health to create knowledge, changing their attitudes towards positive spectrum of health, and decrease the burden of cardiovascular risks in adult life. Through education as an individual they can extend their life expectancy with less ill health (Patton et al., 2016). Educational strategy to reduce the burden of atherosclerosis, to be focused on multidisciplinary lifestyle intervention pneumonic based on "DREAM" which includes healthy diet, relaxation, physical exercise, increase activity and reduce screen time (Lewis et al., 2017), yoga and meditation to decrease stress, increase self-concept for adolescents and aiming to improve long-term health and wellbeing (May et al., 2020). Previous study reported that there was an increased in fast food consumption but non-significant regarding unhealthy snacks among adolescents and concluded that adequate higher dose of interventions may be needed in achieving the goal effectively (Mohammadfarid et al., 2013). Systematic review stated that to reduce risk of CVD including atherosclerosis, strongly linked to behavioural factors, and self-efficacy to make healthy lifestyle choices in adolescents (Smith et al., 2015). Poor healthy diet, sedentary behavior, and lack of physical activity which rise to more number of complications such as obesity, overweight, metabolic syndrome, and hypertension, all those factors contributing to CVD in early adulthood (Nikolic et al., 2011).

The researcher wants to select a younger, healthier generation of middle age adolescence in school, which is a suitable place to initiate primordial prevention (Catalano et al., 2012). So the school will be an ideal setting, with unique individual's to promote positive healthy life choices, enhancing knowledge on preventive measures, transform values and information to the individuals, families, and community (Al Makadma, 2017).

Due to rapid technological advancement there is marked reduction in physical exercise, unhealthy food choices, and increased screen time among the adolescents needed different target behaviors that require different intervention strategies. The benefits of school based interventions on moderate to vigorous physical activity, improve healthier dietary pattern, and decrease sedentary screen time among adolescents include captive audience and wide reach of target group (Hynynen et al., 2016). On the other hand the rights of children obligations states that to recognize the special health and development needs and rights of adolescents and young people (World Health Organization, 2017, 2020). CVDs typically occur in middle age or later, risk factors are determined to a great extent by behaviors learned in childhood and continued into adulthood.

Adolescence provides an opportunity for teenagers to incorporate healthy lifestyle behaviors that will benefit them not only during the teenage years, but also throughout the life span.

## 1.1 Need and Significance of Study

Promoting healthy behaviour during adolescence, and taking steps to better protect young people from CVD risks are critical for the prevention of health problems in adulthood, and for countries' future health and ability to develop and thrive (World Health Organization, 2017). The Rashtriya Kishor Swasthya Karyakram is the National Adolescent Health Programme (NAHP) addresses on to promote behaviour change in adolescents to prevent non-communicable diseases such as hypertension, stroke, cardiovascular diseases and diabetes (Safia, 2016).

The role of community health nurse is expanding and extending care to achieve the Sustained Development Goals (SDGs) 2030 agenda "Leaving no one behind", target – 3 emphasizes to ensure healthy lives and promote well – being for all ages, a 25% relative reduction in risk of pre mature mortality from cardiovascular diseases, cancer, diabetes or chronic renal disease and 10% relative reduction in prevalence of insufficient physical activity (United Nations, 2019).

As a nurse, she can lobby for health promotive measures and mobilize community resources for conducting education and research programme for identifying risk factors among adolescents regarding atherosclerosis. As an educator/research investigator can envisage information, education, and communication to students, colleagues and media regarding risk factors and its preventive strategies. Researcher can empower the community to build up relationship between adolescent and stakeholders, work together, for the achievement of common goals. The overall concept is to develop an integrated programme for the prevention and control of non-communicable diseases as part of primary health care system. The experience of the researcher working in community observed that intervention studies to prevent and cut-off risk factors for atherosclerosis are inadequate; hence the researcher has selected the following study.

Keeping in view of the above-mentioned information, the personal experience of the researcher and the discernment that lecture cum discussion with power point presentation on atherosclerotic risk factors and its prevention, physical activity such as rope skipping, running, stretching exercises through physical education teacher and dietary modification through distribution of pamphlets and monthly once newsletter to parents for enhancing and motivating the adolescence in day to day activities, and will cause a significant reduction in the incidence of the disease, motivated the researcher to conduct structured interventional strategy among the middle age adolescence regarding prevention of atherosclerotic risk factors.

## 1.2 Statement of the Problem

[figure not shown]

Prevention of Atherosclerotic risk factors by Structured Interventional Strategy on knowledge, physical activity, and dietary pattern among middle age adolescence in selected Schools at Arakonam, Tamilnadu, India.

### 1.3 Objective of Study

#### 1.3.1 Aim of study

The main aim of this study is to evaluate the effectiveness of structured interventional strategy on knowledge, physical activity, and dietary pattern among middle age adolescence in selected schools.

#### 1.3.2 Principal Objectives

1. To assess the prevalence of atherosclerotic risk factors among middle age adolescence.
2. To assess the level of existing knowledge on prevention of atherosclerotic risk factors, physical activity, sedentary activity, and dietary pattern among middle age adolescence.
3. To evaluate the effectiveness of structured interventional strategy on knowledge regarding prevention of atherosclerotic risk factors among middle age adolescence.
4. To evaluate the effects of physical activity, sedentary activity, and healthy dietary pattern regarding prevention of atherosclerotic risk factors among middle age adolescence.
4. To compare the relationship between knowledge, physical activity, sedentary activity, and healthy dietary pattern regarding prevention of atherosclerotic risk factors among middle age adolescence.
5. To find the association between pre and post test knowledge, physical activity, sedentary activity, and healthy dietary pattern regarding prevention of atherosclerotic risk factors with selected demographic variables among middle age adolescence.

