|                                             | Details                                                                                                                                                                                                                                                                                                                                                                                                                                                                                                                                                                                                                                                                                                                                                                                                                                                                                                                                                                       | 1 Middle age adolescence who are studying in higher secondary schools aged between 15-17 years at Arakonam. 
 2 Middle age adolescence who are willing to participate in the study 
 3 Able to understand English and Tamil 
 4 Both genders are included in the study 
 5 BMI above 50th percentile
 |

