|                                             | Details                                                                                                                                                                                                                                                                                                                                                                                                                                                                                                                                                                                                                                                                                                                                                                                                                                                                                                                                                                       | 1 Middle age adolescence who are sick
2 Middle age adolescence who are practicing in weight management
3 Middle age adolescence whose sibling or relatives studying in other schools will be selected for the study
4 Middle age adolescence who is below 50th percentile or underweight                         |

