### 1.4 Research Questions

The study is aimed to answer the following questions:

1. What is the prevalence among middle age adolescence in selected schools in Arakonam, Tamilnadu, India?
2. Is there any previous knowledge, physical activity, sedentary activity, and dietary pattern regarding prevention of atherosclerotic risk factors?
3. How could be structured interventional strategy and physical activity improved, reduction in sedentary activity and changes in healthy dietary pattern on prevention of atherosclerotic risk factors among middle age adolescence.

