**Sedentary activity:** It refers to any waking behavior characterized by an energy expenditure less than 1.5 METs while in a sitting or reclining posture e.g., watching television/video, working on a computer for or homework, active commuting to school, Sitting around (chatting with friends / on the phone/chilling) (Hardy et al., 2007; Lewis et al., 2017).

**Atherosclerosis:** Atherosclerotic is a disease condition in which plaque builds up inside the arteries (Smeltzer et al., 2010).

**Atherosclerotic Risk factors:** It refers to the factors responsible for the development of Atherosclerosis of blood vessels in the middle age adolescence. The risk factors are an unhealthy blood cholesterol levels, high blood pressure, smoking, insulin resistance, diabetes, overweight or obesity, lack of physical activity, older age, family history of early heart disease, high levels of C-reactive protein (CRP), high levels of triglycerides, sleep apnea, stress and alcohol. Prevalence of Atherosclerotic risk factors is measured by general appearance, anthropometric measurements, and bio-physiological measurement.

[figure not shown]

**Middle age adolescence:** It refers to boys and girls studying from 10th to 12th standards between the age group of 15 to 17 years among selected schools at Arakonam, Tamilnadu.

**Schools:** It refers to higher secondary schools having students from 10th to 12th standard.

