#### 3.7.3 Sampling technique

Probability stratified random sampling technique will be used for this study. In stratified random sampling, the strata are formed based on individuals' shared attributes or characteristics. Simple random sampling technique (lottery method) will be used to select 3 schools from Arakonam, Vellore District. From the above population 150 samples will be selected from 3 Higher Secondary Schools. 50 samples will be selected from each school. Each class as 5-6 divisions consisting of 45-50 students in each section. One section from each class is randomly selected 15-20 samples who fulfilled the inclusion criteria will be taken as a sample from the particular class. Thus, 150 students are selected from class 10, 11 and 12th standards.

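### The sample is restricted to BMI above the 50th percentile, so it cannot give the school prevalence that objective 1 and research question 1 ask for

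*Protocol*

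**What the plan says.** Section 1.3.2 lists as its first principal objective "To assess the prevalence of atherosclerotic risk factors among middle age adolescence". Section 1.4 asks as its first question "What is the prevalence among middle age adolescence in selected schools in Arakonam, Tamilnadu, India". Section 1.5 defines the group by class, age and place only: boys and girls in the 10th to 12th standards, "between the age group of 15 to 17 years among selected schools at Arakonam, Tamilnadu". The target population in section 3.6.1 also carries no BMI limit.

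The eligibility criteria, given in the registry table and again in section 3.7.2, do carry one. Entry requires "BMI above 50th percentile". The exclusions include "Middle age adolescence who is below 50th percentile or underweight" and "Middle age adolescence who are practicing in weight management", as well as students who are sick. Section 3.7.3 draws three schools and one section from each class, and from these "randomly selected 15-20 samples who fulfilled the inclusion criteria will be taken as a sample". The total is 150, 50 per school.

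Section 1.5 says that prevalence is measured by general appearance, anthropometry and bio-physiological measurement. Section 3.10, Part II, scores these on the study subjects. Its BMI scale marks underweight below the 25th percentile, overweight at the 85th and obese at the 95th.

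**The concern.** The variable used to select the sample is one of the risk factors whose prevalence is to be reported. Students below the cut contribute no data, and they are the ones who cannot be overweight or obese on the BMI scale. Removing them shrinks the denominator and leaves the numerator almost untouched, so the proportion rises. Risk factors correlated with BMI, such as waist circumference and blood pressure, rise with it.

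The protocol describes no survey of all students before the cut, no weighting back, and no recorded screening denominator. An analysis of the 150 alone therefore cannot recover the figure for the schools. If the plan is followed as written, a result for the heavier part of the student body would be reported as the prevalence among 15-17 year-olds in those schools, and a reader could not correct it.

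**Working it through.** The protocol states no expected prevalence, so there is no figure of its own to reproduce. The size of the effect follows from truncation.

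**Inputs from the protocol.** Entry cut: 50th BMI percentile (eligibility criteria). Overweight: 85th; obese: 95th (section 3.10, Part II). Sample: 150 (section 3.7.3).

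**Input not in the protocol.** The share S of local 15-17 year-olds above the reference 50th percentile. It is treated as an assumption below.

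**BMI categories.** For any cut-off c at or above the 50th percentile,

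P(BMI ≥ c | BMI > 50th) = P(BMI ≥ c) / S,

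so the overstatement factor is 1/S.

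- If local students match the reference chart, S = 0.50 and the factor is 1/0.50 = 2.0. Overweight or obese: 0.15/0.50 = 30% in place of 15%. Obese: 0.05/0.50 = 10% in place of 5%.
- If S = 0.60, the factor is 1/0.60 = 1.67.
- If S = 0.40, the factor is 1/0.40 = 2.5.

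**Comparison with sampling error.** At S = 0.50 the bias in overweight-or-obese is 30 − 15 = 15 percentage points. The 95% half-width for 30% in 150 students is 1.96 × √(0.30 × 0.70/150) = 7.3 points, ignoring clustering by section. On that assumption the bias is about twice the nominal margin of error.

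**Weight-management exclusion.** This can work in the other direction. Suppose, at S = 0.50, that it removes a fraction w of students at or above the 85th percentile and no others. The enrolled proportion is then 0.15(1 − w) / [0.15(1 − w) + 0.35].

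- w = 5%: 0.1425/0.4925 = 28.9%, a factor of 1.93.
- w = 20%: 0.12/0.47 = 25.5%, a factor of 1.70.

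**Blood pressure.** Assume BMI and systolic pressure are bivariate normal on the reference scale, with half the students above the BMI cut. The 5% at or above the 95th blood-pressure percentile then reads as 6.6% at a correlation of 0.2, 7.4% at 0.3 and 8.1% at 0.4. The correlations are assumptions, because the protocol gives none.

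**Consistency with the Part II tool.** The BMI band below the 25th percentile is empty at enrolment, since entry requires more than the 50th. The waist scale has its own band below the 25th percentile, which a student above the 50th BMI percentile could still occupy.

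**Largest possible pre-cut denominator.** Section 3.7.3 says "Each class as 5-6 divisions consisting of 45-50 students in each section". Three schools × three classes × one section = 9 sections, and 9 × 45 to 9 × 50 = 405 to 450 students. Age, consent and absence would reduce this.

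**The case against.** The strongest reply is that the stated main aim (section 1.3.1) is effectiveness, and that prevalence is neither a primary nor a secondary outcome in section 1.6. That stands. The pre-post comparisons are made within the enrolled students and are untouched by this point. A reader might infer that the BMI restriction undermines the trial's main conclusions, but nothing in the protocol supports that.

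A second reply is that the registry record describes the study as preventive and screening, and that BMI must be measured before the BMI criterion can be applied, so Part II may be meant for a wider group. This helps only in part. No screening procedure or denominator is described, and Part II is scored on the subjects. Equally, the protocol does not say that whole sections are measured. It takes 15-20 eligible students per class, and measurement could stop once that number is reached, so it cannot be assumed that the pre-cut data will exist.

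A third reply is that the size is uncertain. That also stands. A reader might infer that prevalence will simply double. Doubling requires that half of local students lie above the reference 50th percentile, which the protocol does not say. It applies only to BMI categories, and the weight-management exclusion may reduce it. Nor is every underweight band in Part II empty: that holds for the BMI band only.

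**Conclusion.** The mismatch is real and should be fixed. Objective 1 and research question 1 name all 15-17 year-olds in the selected schools, the sample admits only those above the 50th BMI percentile, and nothing else in the protocol bridges the two.

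The direction for BMI-based overweight and obesity is upward unless the weight-management exclusion removes enough heavier students to offset it. The size depends on an unstated share: a factor of about 1.7 to 2.5 for a share of 60% to 40%, before any allowance for that exclusion. The distortion of blood pressure is smaller and rests on assumed correlations. The damage is confined to one descriptive objective and its research question, which is why this ranks as should-fix and not as a threat to the effectiveness evaluation.

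**What to change.** **Preferred.** Reword objective 1 and research question 1 so that the population is adolescents with BMI above the 50th percentile who meet the eligibility criteria, and make no claim about prevalence in the schools. The cost is a text change in sections 1.3.2 and 1.4.

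**Alternative, if school prevalence is wanted.** Where height and weight are measured in a sampled section to apply the BMI criterion, record them for all consenting 15-17 year-olds in that section before the cut. Estimate BMI-based prevalence from that group, state its denominator, and keep the 150 for the intervention objectives. This needs a paragraph in sections 3.7 and 3.10. It also needs a decision before sampling starts that whole sections are measured, because students not measured then cannot be added at analysis. The 405-450 figure is a ceiling for this group, not an expected yield.

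Measuring waist and blood pressure in non-enrolled students is optional. It would involve up to 450 − 150 = 300 further minors beyond the registered sample and needs its own consent and approval, so it should not be treated as already planned or free. Without it, prevalence of those risk factors should be reported for the enrolled group only.
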